### Design, interventions and setting

### Study design

The proposed study is a 1) block-randomized, 2) 3-arm, 3) multicentric (HUG^3^, Genève; CHUV^4^, Lausanne), 4) national (Switzerland), 5) intervention study.

Blocked randomization is applied to the experimental groups only, blocking for the factors 1) age, 2) gender, 3) COGTEL weighted score [80] and 4) MCI diagnosis (1. amnestic; 2. non-amnestic) to balance both intervention groups for those factors. Experts at the memory clinics will select MCI diagnosed patients for participation.

We use a three-arm design: 2 experimental groups of MCI patients, and one matched passive healthy control group. Except at the level of statistical analyses, no blinding is applied.

The blocked (or stratified) randomization procedure is performed at each site separately, aiming to achieve an equal number of music and psychomotor groups at each site, using Ward’s Hierarchical Agglomerative Clustering Method [126]. We will use this method to establish duplets that are maximally similar with respect to the 4 blocking factors, based on minimum Euclidean distance. Subsequently, an algorithm will attribute randomly one participant of each duplet to each experimental group. So, half of the participants will end up in the music practice intervention (n ~ 16), and the other half in the psychomotor intervention (n ~ 16). A control group of matched (age, gender, education level) healthy controls (n ~ 16) that are not part of the randomization process, will be recruited in Geneva, and will receive financial compensation (gift vouchers).

In the documentation that we will provide to the patients we mention that there are 2 different intervention groups that we want to compare for their effectiveness to improve cognitive and motor function, and that for scientific reasons the repartition to the groups will be determined by chance. We will also mention that if patients refuse to accept their group allocation, they cannot participate in the study.

The psychometric battery consists exclusively of validated tests. Cognitive screening at the HUG and the CHUV is similar. The HUG uses the MMSE score [64] and the Hospital Anxiety and Depression Scale (HADS) [127]. At the CHUV the test used for general cognition is the Montreal Cognitive Assessment (MoCA) [128, 129]; they also use the HADS.

We will cope with test–retest effects by 1) using different versions, or different items, or different order of items of the tests at t0 (baseline, before the interventions), at t1 (after 3 months of interventions) and at t2 (after 6 months of interventions), whenever possible and 2) taking into account the test–retest effects in the healthy passive control group between timepoints.

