### Hypotheses and outcomes

### Main hypothesis

We hypothesize that 6 months of intensive musical practice or psychomotor training will improve or stabilize -each in their own way- general cognitive and physical functioning of MCI patients, compared to the passive control group. Altogether we expect a far stronger effect of musical instrumental practice.

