### Primary Outcome

The primary outcome is increase of the total weighted score at the COGTEL test^1^ [79, 80] at mid-term, after 3 months (t1) and after 6 months (t2) of interventions in the musical practice group and/or the psychomotor practice group of MCI patients compared to baseline and to the passive control group.

The COGTEL served as primary outcome in several recent clinical and epidemiological studies [81–85].

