### Choice of the COGTEL

Although the COGTEL weighted score and the Mini-Mental State Examination (MMSE) [64] correlate at 0.93 [80], the COGTEL covers more cognitive domains (n = 6) than traditional screening tools like the MMSE, which is rather a dementia screening. It comprises 6 subtests covering prospective memory, short- and long-term verbal memory, working memory (digit span), verbal fluency and inductive reasoning.

The COGTEL thus allows a more fine-tuned analysis of cognitive abilities [86]. In addition, test–retest reliability is good (r = 0.85) [80].

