### Specific outcomes according to each intervention 

#### Music practice intervention

Instrumental musical training seems to confer advantages over other types of training in children [32, 99] and elderly [21, 33] and specifically so in MCI patients [62, 65]. Playing an instrument requires both core cognitive components, such as working memory, attention, or processing speed [20, 99, 100], and complex components such as executive functions and even abstract reasoning [20, 21, 34, 101]. Therefore we expect greater advantages in the music group compared to the psychomotor group for the weighted COGTEL score, individual subtests of the COGTEL [79, 80], d2-R test [88, 89], Trail Making tests [90], Go/No-Go [91], visual working memory (fMRI test) [92] and Clock Drawing test [93] (corresponding to Secondary Outcomes no. 1). In addition, sensorimotor function and coordination of the upper body and the hands play a major role and may increase in this group as compared to the psychomotor and control group (Clock Drawing test), Purdue Pegboard test [101, 102]. Emotion regulation may also be enhanced [103], and indirectly impact executive functions.

Functional and structural brain plasticity associated with cognitive and sensorimotor benefits may show in the prefrontal cortex [104–106], the hippocampus [4, 34, 107–109] and sensorimotor areas [110–114], including the auditory cortices [104, 115–117] and also by enhanced functional and structural connectivity [50, 51, 118, 119].

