### Setting

For Geneva participants, music interventions and passage of the behavioral test battery take place at the Geneva School of Health Sciences (Haute Ecole de santé de Genève (HEdS-GE) of the University of Applied Sciences and Arts Western Switzerland (HES-SO)). The psychomotor training takes place at the Department of Psychomotricity (Haute école de travail social de Genève, HETS-GE) of the University of Applied Sciences and Arts Western Switzerland HES-SO, Geneva School of Social work. Brain imaging (MRI) is performed at the BBL, the Brain and Behaviour Laboratory at the University Medical Center of the Geneva University.

For Lausanne participants, all interventions and passage of the behavioral test battery take place at the Leenaards Memory Center of the CHUV, and brain imaging (MRI) will be performed at the Laboratoire de recherche en neuroimagerie (LREN; Laboratory for Research in Neuroimaging) in the same building, also at the CHUV.

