### Before (t0, baseline), after 3 months (t1) and 6 months (t2) of interventions

#### A. Psychometric battery. Total duration: ~75 min. (interrupted by breaks)

D2-R test [88, 89]. Assesses attention, visual scanning accuracy and speed—8 min.Trail making Test A & B [90]. Visuo-motor task, assesses selective visual attention, processing speed and mental flexibility (Shifting)—5 min.Go-No-Go [91]. Inhibition task—5 min.Purdue Pegboard [94]. Evaluates visuo-manual skills and bimanual coordination—10 min.The Clock Drawing test [93] Evaluates apraxia and fine motor control and cognitive functions (visuo-construction, memory, spatial perception/representation, executive functions)—5 min.Laterality recognition test [96]. Assesses right/left judgements of body parts presented by photos on a tablet), evaluates the representation of the body schema- 10 min.Unipedal balance test [95] – < 5 min. Evaluates whole body balance.ERQ: Emotion Regulation Questionnaire [121]—10 min.WHOQOL-BREF [98]—5 min. Assesses well-beingCOGTEL [79, 80]. Provides a main (weighted) score of core cognitive function -10 min.

Nota bene: We will measure the COGTEL first during the prescreening (Supplementary Table 1, PRE-SCREENING STEP 3), then at t1 (3 months) and t2 (6 months) within the psychometric battery.

The Amsterdam Instrumental Activity of the Daily Living Questionnaire (Short Version; (A-IADL-Q(SV)) [97] – 25 min will be first filled in at prescreening, then sent by post at t1 and t2 (filled in with the caregiver, then verified in the laboratory).

A detailed list of the different psychometric measurements is provided in Supplementary Table 2.

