## Data monitoring and quality assurance

Data acquisition and quality is continuously monitored by the experimenters for each patient. A second quality check is performed on the server of the team where all data will be backed up (see Declarations**,** Availability of data and materials) and analyzed by the scientific collaborator (postdoc level) of the research team.

A third checkup is performed by an independent clinical Data Manager (scientific collaborator at PhD level) at the HEdS, who will regularly check all steps of the protocol as accepted by the ethical commissions (randomization, anonymization, inclusion/exclusion criteria, signed informed consent forms, questionnaires, data collection). All source data, documents and outcome data will be available to the monitor, without restriction.

The research team, including a Master student, will meet twice every month to discuss the progress of the study and encountered problems. Any urgent problem will be discussed immediately to assure the quality of the data collection (for instance sudden cognitive deterioration of a patient).

We will report reasons for the withdrawal of individuals for each randomization group and for the passive control group. Exact information on missing data at each time point will be reported in all publications. Missing data will be processed in the analyses with cutting edge means (for instance using the regularized iterative Principal Component Analysis (PCA) algorithm developed by Josse, Husson and Pagès (2009) [164], implemented in the R package missMDA).

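### COGTEL and Clock Drawing are given and scored unmasked at 3 and 6 months although the plan predicts that music will do better on them; masked scoring and, where feasible, masked testers would reduce the bias in music versus psychomotor

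*Protocol article*

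**What the plan says.** The Study design section of the protocol article is explicit: "Except at the level of statistical analyses, no blinding is applied". The article gives no reason for leaving testing and scoring open.

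On the outcome, the Primary Outcome section reads "The primary outcome is increase of the total weighted score at the COGTEL test", assessed at 3 and 6 months against baseline and the passive control group. On content, Choice of the COGTEL says: "It comprises 6 subtests covering prospective memory, short- and long-term verbal memory, working memory (digit span), verbal fluency and inductive reasoning". Clock Drawing is a secondary outcome, both cognitive and sensorimotor.

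The expected direction is stated. Under Main hypothesis: "Altogether we expect a far stronger effect of musical instrumental practice". Under Music practice intervention, for the primary score itself: "Therefore we expect greater advantages in the music group compared to the psychomotor group for the weighted COGTEL score". That sentence goes on to include Clock Drawing, and the Psychomotor intervention section repeats the prediction from the other side.

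Under Setting, for Geneva, "music interventions and passage of the behavioral test battery take place at the Geneva School of Health Sciences"; psychomotor sessions are held at another school. In Lausanne all sessions and all testing share one memory centre. Data monitoring and quality assurance says that the data will be "analyzed by the scientific collaborator (postdoc level) of the research team", without saying whether that person is masked. The article does not say who gives or scores COGTEL at 3 and 6 months.

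**The concern.** COGTEL and Clock Drawing are performance tests given by a person. Prompting, the acceptance of a borderline answer and the rating of a drawing all leave room for judgement. If the tester or scorer knows the arm and shares the team's stated expectation, small differences in handling would favour music, as the hypothesis predicts, and could not be told apart from a treatment effect.

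The contrast most exposed is music versus psychomotor. It is the only comparison protected by randomisation and is planned under both Comparisons and Basic statistical analyses. The plan's other safeguards address different problems. Alternate test versions and correction by the control group deal with retest effects, and masked analysis acts only after the scores exist.

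**Working it through.** **Which scores are exposed.** COGTEL is first measured at prescreening, and its weighted score is one of the four blocking factors. Baseline therefore precedes allocation and cannot carry arm-related bias. The 3- and 6-month scores come after allocation and are exposed.

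**Which contrast is exposed.** The primary objective compares each patient group with healthy controls, who are not randomised and are recruited in Geneva only. A tester can often tell a healthy control from a patient, so hiding music versus psychomotor does little for that contrast. It acts on the randomised one.

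**Illustration of size.** The plan has no figure for this bias to reproduce.

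Inputs:
- *n* = 12 per arm, the minimum number of completers (Attrition / Drop-outs). As a check, the plan's effect size is f = √(0.296/0.704) = 0.648. A two-group one-way comparison with f = 0.65 has power 0.826 at 11 per group and 0.861 at 12, so 12 per arm is consistent with the plan's power statement.
- Two-sided alpha 0.05 (Basic statistical analyses).
- Baseline correlation r from 0 (no adjustment) to 0.85. The upper value is COGTEL test–retest reliability (Choice of the COGTEL). The plan incorporates baseline scores, but the correlation over 3 to 6 months in patients under training is not given and may be lower than 0.85.
- Shift b towards music of 0.2 or 0.3 SD. This is an assumption; the documents give none.

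Formulas, in units of the COGTEL SD:
- SE = √(2/n) × √(1 − r²)
- Noncentrality = b / SE
- False-positive rate = P(|T| > critical value), with T noncentral t. Degrees of freedom are 22 without adjustment (critical value 2.074) and 21 with baseline as covariate (2.080).

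Worked case, r = 0.85: SE = √(2/12) × √(1 − 0.7225) = 0.408 × 0.527 = 0.215. For b = 0.2, noncentrality = 0.2/0.215 = 0.93 and the rate is 14.4%.

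| r | SE | b/SE at 0.2 SD | rate | b/SE at 0.3 SD | rate |
|---|---|---|---|---|---|
| 0 | 0.408 | 0.49 | 7.6% | 0.73 | 10.8% |
| 0.5 | 0.354 | 0.57 | 8.4% | 0.85 | 12.8% |
| 0.7 | 0.292 | 0.69 | 10.0% | 1.03 | 16.6% |
| 0.85 | 0.215 | 0.93 | 14.4% | 1.39 | 26.5% |

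Rounded, this is about 8–14% for 0.2 SD and 11–27% for 0.3 SD. A larger sample does not help: at 16 per arm without adjustment the rates are 8.5% and 13.0%, because the standard error falls and the bias does not. This is a single-visit calculation standing in for the planned mixed model.

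**What can still be masked.** Ten first-wave patients have completed, which is 10/32 = 31% of the planned 32. Under the stated schedule the third wave has baseline from August 2022 and runs to April 2023, so its 3- and 6-month visits are the natural place for a change.

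**The case against.** The strongest counter-argument concerns what the article does not say. It never states who administers or scores COGTEL after baseline, so a reader might infer that testers are documented as knowing each patient's arm. That is a fair inference from the absence of blinding, but it is not stated. Nor does sharing a school with the music sessions in Geneva show that testers watch them, and in Lausanne both trainings and the testing share one centre.

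A reader might also infer that masking would remove the bias at almost no cost. The documents do not support this. Patients know their training and may mention it, and the research team meets twice a month about progress. Recruitment refers to a single clinical psychologist who explains the randomisation procedure to patients; if that person also tests, masking is harder. The article gives no staffing figures, and nothing shows that the two sites could cover for each other.

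A third tempting reading is that the primary result is undermined and that masking would rescue it. The primary contrast is with healthy controls, where masking between the two trainings helps little. Finally, a normal approximation at r = 0.85 alone would give about 15% and 29%. Those figures slightly exceed the t-based top of the range, and both r and the shift are assumed.

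These points limit the size of the claim and the remedy. They do not answer the central one: the plan chooses open assessment, predicts the direction on the same scores, and offers nothing that offsets it.

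**Conclusion.** The point holds in a limited form. Unmasked administration and scoring of COGTEL and Clock Drawing at 3 and 6 months leave the only randomised contrast open to bias in the predicted direction, and masked analysis does not cure it. The illustrated error rates above rest on an assumed shift, an assumed baseline correlation and no true difference. They show sensitivity and do not estimate what will happen. Masking would reduce this bias, not remove it. It is worth doing where it can still be done, and should be done rather than being a condition for the trial to proceed.

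**What to change.** For the remaining 3- and 6-month visits:
- Withhold the allocation list from the existing testers and keep them out of training sessions, where feasible.
- Ask patients before testing not to mention their activity.
- Record the tester's guess of arm after each visit.
- Have coded COGTEL and Clock Drawing record sheets scored without arm label by existing staff who are masked to arm. Include sheets from earlier visits if they were kept; the article does not say whether they were. Name the scorer's role and confirm that this person is masked, since the article does not say so of the team member who analyses the data.
- State in the report which visits were tested or scored unmasked, and give this as a limitation.

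This needs no extra patients or visits and does not change the sample size. Masked scoring can draw on existing staff, provided someone on the team is masked. The cost is in scheduling, coding of sheets and a short written procedure; the article gives no figures from which to price it. Some patients will reveal their arm, masked scoring does not correct prompting during the test, and completed visits, including those of at least the ten first-wave patients, remain tested unmasked.

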### Withdrawal and discontinuation

As mentioned in the informed consent form, patients can withdraw from the study at any time without providing a motivation.

If there is a suspicion of sudden cognitive impairment or the start of dementia, memory centers' professional medical doctors will validate or refute this suspicion. Whether patients may pursue interventions, if they so wish, will be determined on an individual basis by those specialists in agreement with the principal investigator of the study.

In the case of withdrawal, in the file containing the code and personal information of the patient, the date and motivation (or absence of motivation) will be mentioned, and the data of this patient will be excluded from the analyses.

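### The rule that patients who refuse their allocated group cannot take part permits arm-aware exclusion after randomisation from the only randomised comparison

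*Protocol article*

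**What the plan says.** All references are to the protocol article.

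- **Study design, the rule.** "We will also mention that if patients refuse to accept their group allocation, they cannot participate in the study." It follows the statement that patients will be told that chance decides their group.
- **Study design, what is randomised.** "Blocked randomization is applied to the experimental groups only." The healthy controls stand outside the randomisation.
- **Study design, how.** Patients are paired on age, gender, COGTEL weighted score and MCI type. "Subsequently, an algorithm will attribute randomly one participant of each duplet to each experimental group."
- **Study design, blinding.** "Except at the level of statistical analyses, no blinding is applied."
- **Psychometric battery.** "We will measure the COGTEL first during the prescreening", with t1 and t2 to follow. The prescreening step named there is the first laboratory visit.
- **Recruitment, prescreening and informed consent procedures.** Randomisation is explained by telephone and again at the first visit. Consent is validated at that visit if the patient still agrees and meets the criteria.
- **Withdrawal and discontinuation.** The date and any stated reason are recorded, and "the data of this patient will be excluded from the analyses."
- **Data monitoring and quality assurance.** "We will report reasons for the withdrawal of individuals for each randomization group and for the passive control group." Missing data are to be imputed.

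**The concern.** The two arms are very different activities, and patients know which one they have drawn. Those who turn down music need not resemble those who turn down psychomotor work. They may differ in musical interest, mobility, confidence or apathy, and such traits can bear on cognitive change and on home practice. Preference is not among the four blocking factors, so blocking does not protect against this.

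If decliners leave both the study and the dataset, the music versus psychomotor contrast compares people who accepted music with people who accepted psychomotor training. It no longer compares the groups that chance created. That contrast carries the expectation, stated under Main hypothesis, of a far stronger effect of music. The mixed model and the planned imputation cannot repair it, because neither acts on patients who have been removed.

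**Working it through.** **Step 1: when can an allocation be refused?**
1. COGTEL is taken at the first laboratory visit, and consent is validated at that visit.
2. COGTEL is one of the four variables used to form duplets, so duplets come after that visit.
3. The random draw is made within duplets, so an individual allocation comes later still.

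Anyone with an allocation to refuse has therefore consented, been screened and been randomised, and has a baseline score on the primary outcome. Without blinding, the refusal is made knowing the arm.

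**Step 2: what happens to that patient's data?** Study design says the patient cannot participate. If this is handled as withdrawal, the data are excluded from the analyses. No section keeps such a patient in follow-up or in the analysis.

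**Step 3: is lost power the main harm?** The article's own figure comes first.
- Partial η² of 0.296 gives f = √(0.296/0.704) = 0.648, which agrees with the stated 0.65. For two groups d = 2f = 1.30.
- A two-sided two-sample t-test at 0.05 needs 11 per arm for 80% power (0.826). With 12 per arm the power is 0.861, so the stated n = 12 is reproduced closely if read as a per-arm number.
- With 12 versus 10 patients, power at d = 1.30 is still 0.823.

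At the article's assumed effect, a few refusals cost little power. The issue is selection.

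**Step 4: how large could the selection be?** Every input here is an assumption, because the article gives neither a refusal rate nor a difference between refusers and acceptors.
- *Refusal in one arm only.* If a share p refuses, the acceptors' mean differs from the full arm's mean by p × (acceptor mean − refuser mean). With 2 of 16 refusing and a 0.3 SD difference: 0.125 × 0.3 = 0.04 SD. With 4 of 16 and 0.8 SD: 0.25 × 0.8 = 0.20 SD.
- *Refusal in both arms, driven by preference.* Suppose preference for music is normally distributed, correlates ρ with COGTEL change, and each arm loses the share r that likes it least. With no true effect, the bias in the contrast is 2ρφ(z_r)/(1 − r), where φ is the standard normal density and z_r the r-quantile.

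| ρ | r | Bias (SD) | Analysed per arm | Actual type I error at nominal 5% |
|---|---|---|---|---|
| 0.2 | 10% | 0.08 | 14 | 5.5% |
| 0.5 | 20% | 0.35 | 13 | 13.7% |

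- *Scale.* The standard error of a two-arm contrast with 16 per arm is √(2/16) = 0.35 SD.
- *Duplets.* At an assumed 10% refusal, 16 × 0.9² = 13 of 16 duplets are expected to stay intact. At 20% it is 16 × 0.8² = 10.

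**The case against.** The sentence describes patient information and can be read as a condition of consent: join only if either arm is acceptable, with no switching. Randomisation is explained twice before consent is validated, which should deter many refusals, and a ban on switching protects the comparison. This stands in part. But the text speaks of refusing an allocation, does not confine the rule to the time before the draw, and describes no recorded acceptance of either arm.

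It is also fair to say that most of the analytic harm comes from the withdrawal rule, and that correcting that rule would remove much of the problem.

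Four stronger readings are tempting, and the article does not support them.
- **Refusals would go uncounted because a refuser never becomes a participant.** A refuser has already consented and most naturally falls under withdrawal, with a recorded reason and reporting by randomisation group. Unreported refusals are an inference.
- **Refusers cannot be replaced.** The statement under Attrition / Drop-outs rests on interventions being ongoing, so it concerns losses during training. Later waves were recruited towards 16 per group.
- **The primary comparison loses its randomised basis.** The stated primary outcome compares each patient group with baseline and with the non-randomised healthy group. Music versus psychomotor is a further contrast, though an important one.
- **Broken duplets invalidate the analysis.** No pair-matched analysis is specified, and baseline scores enter the models.

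**Conclusion.** The point holds as a fault in a stated rule. Taken together, the allocation rule and the withdrawal rule allow arm-aware removal of randomised patients from the only randomised contrast, and nothing in the article brings them back.

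Its size cannot be stated. A reader might take 0.04 to 0.20 SD, or 0.08 to 0.35 SD under the preference model, as estimates; they only show what the assumed inputs would produce. The article's only evidence is the first wave, under Recruitment, practical details. Of 14 consenting patients, 4 stopped: 2 for early dementia, 1 for health and 1 for personal reasons. None is attributed to allocation, and only the last, 1 of 14 (7%), is worded loosely enough that it could be. The case for change rests on how cheap the correction is, not on a demonstrated bias.

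**What to change.** 1. **Before the draw.** Keep the ban on switching arms. Record explicit acceptance of either arm before duplets are formed, and do not randomise patients who would accept only one. This moves most refusals to where they do no harm to the comparison.
2. **After the draw.** Count everyone allocated by the duplet algorithm as randomised in the allocated arm. Report those who decline the allocation by arm, as a category of their own.
3. **Follow-up.** Invite decliners to the t1 and t2 psychometric tests, at least COGTEL; MRI need not be asked of them. This matters because a patient with only a baseline score adds nothing to a mixed model that uses baseline as a covariate.
4. **Analysis.** Retain their available data in an as-randomised mixed model for music versus psychomotor. Reconcile Study design with the exclusion of data under Withdrawal and discontinuation and with the missing-data handling under Data monitoring and quality assurance.

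**Cost.** Changes to the protocol and patient information, which can help only the remaining enrolment; test visits for a few patients; and slight dilution of the effect from untrained patients kept in their arm. The as-randomised analysis and the by-arm reporting can be applied to all waves.
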